### Study design, setting and participants

This research will be conducted in the Audiology Clinic of Rehabilitation School of Iran University of Medical Sciences.

This study consists of two main parts. Part 1: develop and determine an informational masking measurement test and explain its validity characteristics in a test development study, conducted cross-sectionally. The study population will be a group of elderly (60 to 75 years old) and a group of young (20 to 40 years old) people. The young people will be recruited from rehabilitation students of Iran University of Medical Sciences, while elderly people are those referred to the audiology clinics of Iran University of Medical Sciences.

Part 2 (simple randomized clinical trial): the effect of training on informational masking release. This part of study is a simple randomized clinical trial design and patients will be randomly assigned into two groups of control (not receiving auditory spatial training) and intervention (receiving auditory spatial training). The random allocation will be performed based on balanced randomization [1:1] where the allocation will be applied by random number table (those assigned an odd number, control group; those assigned an even number, intervention group). This allocation sequence will be generated by one of the audiology clinic staff of the IUMS who will not have any role in the study. An elderly population, 60–75-years-old, who are referred to the audiology clinics of Iran University of Medical Sciences will be selected. The two groups will be matched for age and gender. Those in the control group will not receive any rehabilitation programs during the study.

*Inclusion criteria (for all participants in the study):* auditory thresholds ≤25dB within the 250–8000Hz frequency range for ensuring the normal pure tone audiogram or normal peripheral hearing, ensuring lack of salient cognitive problems using Mini Mental State Examination (MMSE)
^26^; having diploma or higher degree; right-handedness (using Edinburgh handedness inventory); speaking Farsi and being monolingual; complaint about speech in noise perception difficulties (just for those in part 2 of the study); and normal condition of middle ear function.

*Exclusion criteria (for all participants in the study):* unwillingness for participation in each step of research and not meeting inclusion criteria.

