*In the presence of meaningless competing signal:* the previous signal will be manipulated such that its spectrum content remains fixed but meaningless - indeed, energetic masking will remain but informational masking will be reduced. "Time-reversed speech" will be used for this purpose. This is one of the most effective methods in behavioral and neurophysiological research performed for the effects of speech signals on each other. In this method, by fixing the long-term acoustic spectra of two signals and manipulating one of them such that it divides into non-overlapping time segments, and with reverse time presentation of each segment connecting them to each other, we will have a signal which is equal with the first signal in terms of the spectrum but is not understandable
^28^. In the case of using 20–40 millisecond time windows, this method does not have significant effectiveness in non-understanding the speech signal; therefore, longer time windows should be used
^28^. MATLAB R2018 software will be used in constructing this signal.

The intensity setup of the speech signals with two competing talkers used were similar to some previous studies
^29^. The overall level (RMS power) of target CRM was fixed at the 60 dBSPL. The overall level (RMS power) of each masker was adjusted relative to the target’s level to produce one target-to-masker ratios (TMRs). Initially the masker level was varied in 4 dB steps and then they varied adaptively in 2 dB steps. The two CRM masker phrases always had the same RMS power. The TMRs in sentence recognition test in steps A and B was ±8, ±4, and 0. The target signal is always presented from a loudspeaker in the 0-azimuth degree and two competing signals from the loudspeakers, which are at ±45 and ±90 degree and 0 azimuth degree (once with spatial separation and twice in the direction of target signal), where once the competing signal has the same gender as the target signal and another time has a different gender. As a result, 30 conditions will be evaluated at each step (5 TMRs and three spatial angles with two different genders).

Finally, the informational masking score in all 30 conditions will be calculated as follows:

Speech recognition score in the meaningful competing noise condition-speech recognition score at non-understandable noise condition=informational masking score (percentage).

Jakien and Gallun provided mathematical equations by which the effects of age can be predicted for 45 degrees of separation

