^30^. We will develop similar equations, compare them with the published equations, and will use these normative functions to assess improvements in performance after training.

In this step of the research, construct validity will be used to determine the validity of the test. For this purpose, Speech, Spatial, and Qualities of Hearing Scale (SSQ) questionnaire score of each individual will be compared against the informational masking score
^31^.
Figure S1 (Extended data) represents the participant’s timeline of the first part of the study.

***Part 2: the effect of auditory spatial training on the informational masking release.*** This part of research will be conducted in three steps: before auditory spatial training, during training, and after training.

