### Data analysis

Central tendency and dispersion indices (mean and standard deviation) will be used in descriptive analysis of data. In data analysis and for determining the reliability of the Persian version of the coordinate response measure (CRM) corpus, paired t-test and Pearson correlation will be used in the case of normality of data; otherwise, Spearman test will be employed, and one-way ANOVA will be utilized for determining intra-class correlation coefficient.

In part 2 of the research, repeated measures ANOVA values will be used for inter-group comparisons and two-way ANOVA will be employed for comparison among groups. SPSS software (V20.0, IBM Corporation, New York, USA) will be used for statistical data analysis and the significance level for all tests will be 0.05.

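### The Part 2 arms are described as matched on age and gender, but the named analysis has no term for either, which costs precision if the matching is real and the variables are prognostic

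*Protocol article*

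**What the plan says.** Four statements in the protocol article bear on this point.

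- **Study design, setting and participants**, on Part 2: "The two groups will be matched for age and gender". No method of matching is given.
- **The same section**, on how participants reach their arm: "the allocation will be applied by random number table (those assigned an odd number, control group; those assigned an even number, intervention group". The design is called simple, the ratio is 1:1, and no pairs or strata are mentioned.
- **Study procedures, Part 1** refers to published "mathematical equations by which the effects of age can be predicted for 45 degrees of separation". The investigators plan similar equations of their own and "will use these normative functions to assess improvements in performance after training".
- **Data analysis**, for Part 2: "repeated measures ANOVA values will be used for inter-group comparisons and two-way ANOVA will be employed for comparison among groups". The factors of the two ANOVAs are not listed. No covariate, pair or stratum is named, and the age-based functions are not mentioned.

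**The concern.** When a design forces the arms to agree on a variable that predicts the outcome, that variable can no longer contribute to the difference between the arms. If the model omits it, its variance still sits in the residual. The standard error then overstates the real sampling error of the matched comparison, so the test is conservative and the interval is wider than it need be. The usual rule is that variables constrained by the design go into the analysis.

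Here the design section constrains age and gender, the Part 1 procedures treat age as predictive, and the analysis section names neither. With 36 people planned, a 10% change in interval width matters. If the matching is not carried out, the omission has a different and milder effect: explainable variance and chance imbalance between two arms of 18 are left unaddressed.

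**Working it through.** **Inputs from the protocol article.**
- 18 per arm (Sample size, Part 2). This follows from 14/(1 − 0.20) = 17.5, rounded up. The 14 itself does not follow from the stated inputs: the standard formula with a squared denominator gives 49.7. That is a separate matter, and nothing below relies on it.
- Standard deviations of improvement 25.17 and 18.15 (Sample size). Root mean square: √[(25.17² + 18.15²)/2] = √(962.95/2) = 21.94.
- Two-sided 5% level (Data analysis; Z = 1.96 in Sample size).

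**Assumption.** R² is the share of the within-arm variance of the analysed outcome that age and gender explain. The documents give no figure, so 0, 0.10, 0.20 and 0.30 are shown.

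**Step 1: interval width if the arms are matched.** The half-width of the 95% interval for the difference in change is

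- unadjusted: t(0.975; 2n − 2) × SD × √(2/n) = 2.0322 × 21.94 × √(2/18) = 14.86;
- with age and gender: t(0.975; 2n − 4) × SD × √(1 − R²) × √(2/n), where t(0.975; 32) = 2.0369.

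| R² (assumed) | Adjusted half-width | Ratio to 14.86 |
|---|---|---|
| 0 | 14.90 | 1.002 |
| 0.10 | 14.13 | 0.951 |
| 0.20 | 13.33 | 0.896 |
| 0.30 | 12.46 | 0.839 |

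The ratios do not depend on the SD or on the size of the treatment effect.

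**Step 2: is the unadjusted interval valid?** This was simulated for the change score, 18 per arm, one covariate and 8,000 replicates per setting. Nominal coverage is 95%.

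| Setting | Unadjusted coverage | Unadjusted width relative to adjusted |
|---|---|---|
| Matched; covariate predicts change, R² about 0.10 | 96.0% | 5% wider (0.707 vs 0.672) |
| Matched; covariate predicts change, R² about 0.30 | 98.1% | 19% wider (0.802 vs 0.674) |
| Matched; covariate affects level only | 95.0% | equal (0.673 vs 0.673) |
| Unmatched; covariate predicts change, R² about 0.10 | 94.7% | 4% wider (0.708 vs 0.684) |
| Unmatched; covariate predicts change, R² about 0.30 | 94.9% | 17% wider (0.800 vs 0.681) |

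The interval is over-wide in the coverage sense only when the arms are matched and the covariate predicts the quantity tested. Under unmatched allocation coverage is nominal, and adjustment only buys precision.

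**Step 3: cost of adjusting for nothing.** If neither variable predicts the outcome and the arms are matched, the interval widens by about 0.2% (Step 1). If the arms are unmatched, chance imbalance adds to the cost. Simulating age uniform on 60–75, gender 50:50 and R² = 0 gives an adjusted/unadjusted width ratio of 1.03 at 18 per arm and 1.05 at 14 per arm.

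**The case against.** The strongest reply has four parts.

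**The analysis text is brief.** It names no factors at all, not even group and time, and a condensed article may leave covariates to a fuller plan. This stands in part: the text does not say that age and gender are excluded. But it does name the models, and a two-way ANOVA with group as one factor cannot hold both age and gender as well. The design section states a constraint that the named methods do not take up.

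**The described allocation produces no matching.** Odd/even assignment from a random number table balances nothing by design. This stands. A reader might infer that the Part 2 intervals simply are too wide and the test conservative. The documents do not support that, because under the only allocation mechanism described the unadjusted interval has nominal coverage.

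**Age may affect level and not change.** The sample size section defines the studied variable as change, and a stable age effect on level cancels in the group-by-time contrast. This also stands. The cited equations concern age effects on performance at 45 degrees of separation, and nothing says that age predicts training gain within 60–75 years. Still, the Data analysis wording does not confine the test to the group-by-time contrast. A between-group effect on score levels would not cancel age, and the protocol itself links the age-based functions to improvement after training.

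**Gender is not shown to be prognostic.** The document gives no effect of listener gender; the gender it discusses in the test and the training is that of the talkers. This stands. The case for a gender term rests only on its being named as a matching variable.

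**Conclusion.** The point holds conditionally. The protocol names age and gender as matching variables and treats age as predictive, while the stated Part 2 analysis has no term for either. If balance is enforced and the variables predict the outcome analysed, adjustment would narrow the interval by about 5%, 10% or 16% at R² of 0.10, 0.20 or 0.30, all assumed. If allocation is simple and unmatched, the unadjusted analysis is valid and the loss is one of efficiency. If age acts only on level, the group-by-time contrast gains nothing.

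A reader might go further and conclude that the trial discards power it has already secured through matching. That does not follow. The sample size formula is for independent groups and credits neither matching nor covariates, and the documents give no R² from which to compute a gain. In either case the possible error is loss of precision, not a false positive.

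**What to change.** 1. In Study design, setting and participants, reconcile the matching statement with simple randomisation. Either state how balance on age and gender is enforced (pairs or strata), or withdraw the word matched and describe the allocation as simple.
2. In Data analysis, name age (continuous, in years) and gender as prespecified terms in the Part 2 between-arm model for the informational masking score, and likewise for synthetic sentence identification, SSQ and reading span. If pairs or strata are used, put those same factors in the model.
3. State how the age-based normative functions enter the assessment of improvement, or that they are descriptive only.

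The cost is a few sentences and two degrees of freedom for age and gender. Both variables must be known in any case if the arms are to be matched on them. The worst case is an interval about 3–5% wider, if the arms are unmatched and neither variable is prognostic. Study status says that allocation has not yet been performed, so the terms can be fixed before any outcome comparison.

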### Ethical statement and consent to participate

The Medical Ethics Committee of Iran University of medical sciences approved the study protocol (IR.IUMS.REC.1397.303) and the ethical principles of the ethics committee will be observed in this research. Researchers will send any amendments to the protocol in the future to the ethics committee.

One of the researchers of this study will obtain written informed consent from patients willing to participate in the trial (see Extended data). The purpose of the research and its steps will be explained for all participants before the study start. Confidentiality of data and results of tests will be ensured to participants. Participants will be made aware that they can refrain from cooperation in the study when they want. Conducting tests has no side-effects for the studied individuals and all tests and training sessions will be without cost to the participants.

Since this will be the first time of performing this training, we will running a focus group and asking our participants what they will think of the intervention and how likely they will continue performing the auditory training in the future.

To promote participant retention and complete follow-up, in every training session the examiner will provide feedback to all participants and will inform them about the training progress. The researcher will ask them about the impact of training on the participant’s daily communication conversations. Also at the first of each training session the initial level of training will be calculated and if there will be a progress in the initial signal to noise ratio which train will be started from that, the examiner will inform the patient.

All data will be entered into forms which are prepared for data collection (see
Table S2; Extended data) and the participant files will be stored at study site and will be maintained in a secure place and manner. Participant files will be maintained in storage for a period of 2 years after completion of the study. Only Principal Investigators will be given access to the study data.

### Dissemination

The study outcomes will be published through peer-reviewed journals. The data resulting from this study will be released to the audiologists and participants and the general medical community. The results of this trial will be communicated to the external funding body through a formal report. There is no limit in the publication of the trial results.

### Study status

The study started in December 2018 and will continue until December 2019. To date, the enrolment of the patients has been performed and the allocation will be performed in the near future.

## Discussion

Since there is a progressive increase in elderly populations around the world, the independence of this age group has gained much attention, and Iran is no exception
^45^. One of the most important points in independent life during aging is the capability for effective verbal communication. Unfortunately, this capability declines in elderly people, especially tracking speech in environments where several speakers talk with each other. Most elderly individuals complain that despite good hearing, they cannot understand speech in noisy environments
^1^. Indeed, elderly people cannot use auditory spatial signs for informational masking release due to the reduction of their auditory processing and cognitive abilities
^11,
12^. Since informational masking has an important role in competing signal environments and rehabilitation programs have not considered this an important aspect of masking, designing training that can help elderly people in releasing this masking is novel. Therefore, if the main research hypothesis, i.e. auditory spatial training can improve informational masking release in the elderly people, is confirmed, by providing the therapeutic solution in this age group, a series of auditory spatial trainings based on informational masking release will be provided for audiologists. In addition, the Persian version of the coordinate response measure (CRM) corpus and its reliability and validity will be calculated to be used in research on speech recognition in noisy environments.

## Data availability

### Underlying data

No data is associated with this article.

### Extended data

Open Science Framework: The effects of auditory spatial training on informational masking release in elderly listeners: a study protocol for a randomized clinical trial.
https://doi.org/10.17605/OSF.IO/SDEJP
^46^.

This project contains the following extended data:

Table S1: The questionnaire of content and face validity of Persian version of coordinate response measure (CRM) corpusTable S2: The data collection sheet for the second part of the studyFigure S1: Participant timeline for part 1 of the study (Developing an informational masking measurement test and determining its validity)Figure S2: Participant timeline for part 2 of the study (the effect of auditory spatial training on the informational masking release)Informed consent form for the participants of the first part of the studyInformed consent form for the participants of the second part of the study

Data are available under the terms of the
Creative Commons Zero "No rights reserved" data waiver (CC0 1.0 Public domain dedication).

### Reporting guidelines

Open Science Framework: SPIRIT checklist for ‘The effects of auditory spatial training on informational masking release in elderly listeners: a study protocol for a randomized clinical trial’:
https://doi.org/10.17605/OSF.IO/SDEJP
^46^.
